### Participant recruitment

The permission to conduct the study was sought, and relevant approvals were obtained from the Permanent Secretary (PS) of the State Primary Boards, Permanent Secretaries of State Health Districts, Director of Nursing Services and the Director of Community Services. Nurses who are in the dental and maxillofacial unit and/or nurses who have assisted with Smile Train education and surgeries were excluded. The nominal rolls of nurses and community health workers in the State Health Districts served as the sampling frame, and five nurses and five community health workers who met the selection criteria were selected from each district by simple random sampling (balloting). To avoid contamination, participants from Health districts who were from more distant locations were selected for the control group, while the participants from locations closer to the training center were selected for the intervention group. Following the IRB approval from the Ethics Committee of the participating centers, each recruited participant signed a written consent before active recruitment into the study.

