### Intervention and control

The intervention and control groups will consist of participants selected by a non-random process but with comparable characteristics. Across the three study sites, a total of 60 PHC workers (20 Nurses and CHWs at each site) will be assigned to the intervention group, and a corresponding number of participants will constitute the control group. Participants in the control group will receive a one-off conventional oral health education session consisting of a lecture on oral health, tooth brushing, and diet and oral hygiene demonstration using dental models. The intervention group will be exposed to the week-long pilot training on oral health education delivered by designated trainers (see Table 2). They will also participate in group activities such as oral exams and activity sheets. Each module is expected to last for approximately 4 h. Participants in the intervention group (those who will be trained) will be compared to the control group at each study site. Before the training begins, each participant will be administered a pre-intervention questionnaire to evaluate their oral health knowledge at baseline. The assessment will be repeated immediately after training and after 3 months. These evaluations not only serve as a means of monitoring training impact but also allow participants to observe how they improve throughout the training.

**Table 2 tab2:** Program and module delivery for the five-day training.

Day	Module
Day 1	Pre-intervention test Introduction to oral health
Day 2	Introduction to oral diseases and conditions
Day 3	Techniques in oral health promotion and oral disease prevention
Day 4	School and community-based oral health promotion
Day 5	MCOH Post-intervention test Facilitator assessment of participants capability to provide oral health education.

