### Program assessment/evaluation

The assessment of the study outcome will be performed using a quantitative and a qualitative approach. Quantitative assessment will be conducted using questionnaires administered by the designated trainers, and the data will be fed into the Qualtrics software for data management. Before the training commences, all participants will take the pre-intervention test that measures their initial knowledge of oral health. The questions will be co-developed by Dental Public Health (DPH) consultants and educators on the research team based on available evidence and will be assessed for face and content validity before deployment. The questionnaire will also be pre-tested among participants who would not be involved in the study. The control group will be immediately provided with the post-intervention evaluation after the one-day lecture. After the training, participants in the training group will be assessed using the post-test. The pre and post-test scores will be compared for participants in the treatment and control groups. Participant’s capability to screen and detect oral diseases will be assessed post-intervention using picture tests.

After 3 months, a follow-up evaluation will be conducted. The number of logged referrals from the PHCs to the dental centers for oral health conditions will also be assessed for 3 months post-training based on the information logged by these providers (see Logic Model-Table 1). In addition, 5% of patients who were referred to dental centers as entered in the logbooks will be contacted via phone calls to verify their final visit to the dental centers.

The qualitative assessment to assess the impact of the training, points of improvement and the practicability of incorporation of oral health promotion activities into maternal and child health visits will be conducted with select participants in the intervention group at the 3-month evaluation using Deliberative Focus group discussions. This approach to evaluation serves to enhance program feedback through participants’ experiences and opinions. Refresher training will be conducted accordingly in month three if necessary. Data collection will be from February to May 2024.

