## Discussion

Pilot studies are essential for improving the quality and efficiency of the major study (49). Thus, the success of this pilot program could help set the foundation for sustained oral health education training for primary health care workers, invariably creating a pool of qualified peer trainers for PHC workers, PHC patients, their families, and the general population. Studies have shown how misinformation, myths and cultural beliefs among individuals and community stakeholders negatively impact oral health attitudes and care-seeking behaviors in developing countries (50–54). Promoting approaches where qualified care professionals provide adequate and accurate oral health information may thus influence positive oral health practices, leading to improved oral health and overall health. The scope of the current project will encompass most of the essential components of primary oral care recommended by the WHO by leveraging the strategic positioning of the PHC system and its link with individuals, communities, and the health care system. These recommendations include “*age-friendly primary health care for oral health, maternal and child oral health care, health communication/oral health education, disease prevention methods, early detection, pain control - emergency care for oral health, continuity of oral healthcare, supportive referral systems and priority to those people most in need*” (7). The strength of the QED approach lies in its simplicity regarding data collection, ease of implementation and associated low cost (55). However, there are some limitations to this study design. Due to non-randomization of study participants, other factors related to the outcome of interest beyond the control of the researchers could potentially influence study results (56). Secondly, it is impossible to determine causality because quasi-experimental research is not an actual experiment; thus, only associations between interventions and outcomes can be made (43). Furthermore, because the treatment and control groups are nonequivalent (group assignment is by non-random selection), selection bias may exist. The presence of a nonequivalent no-treatment control in this study reduces issues such as threats to internal validity (i.e., observing the same participants over time). This is due to the assumption that the presence of similarity between the treatment and the control groups at baseline reduces the likelihood of having significant confounder differences between both groups (55, 57, 58).

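### Arm is set by distance from the training center, so training and location cannot be separated, and the stated comparability of the groups does not follow from the selection rule

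*Protocol article*

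**What the plan says.** Participant recruitment gives the allocation rule in two halves: "participants from Health districts who were from more distant locations were selected for the control group", and "participants from locations closer to the training center were selected for the intervention group". The stated reason is to avoid contamination. Within each district a ballot picks five nurses and five community health workers. That is random selection of people, not random assignment to arm.

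Intervention and control then describes the two groups as "participants selected by a non-random process but with comparable characteristics". No matching or balancing step is described.

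The Discussion concedes that "because the treatment and control groups are nonequivalent (group assignment is by non-random selection), selection bias may exist". It goes on to argue that internal validity is helped because "similarity between the treatment and the control groups at baseline reduces the likelihood of having significant confounder differences between both groups". Distance is not named as a source of bias.

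The hypotheses cover knowledge scores and referral practices. Knowledge is tested before training, immediately after and at 3 months. For referrals, Program assessment/evaluation says: "The number of logged referrals from the PHCs to the dental centers for oral health conditions will also be assessed for 3 months post-training". No count before training is described.

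**The concern.** A non-randomized comparison needs some reason to believe that the groups would have fared alike without the training. Here the only stated rule makes them differ systematically on one feature, location, in the same direction at every site. The comparability statement and the similarity argument are therefore assumptions that the selection rule works against.

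The outcome most exposed is referrals. The Introduction says that rural communities in Nigeria have hardly any access to oral care. If the more distant districts also have fewer dental centers within reach, their workers would have less reason to refer, and the trained arm would log more referrals even if the training changed nothing. The pretest, as described, measures knowledge, so it would not reveal this. The pilot is also meant to inform the sample size of the main study, so a distorted contrast could carry forward.

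**Working it through.** **Inputs from the article.** 20 workers per arm per site, three sites (Participants; Intervention and control); a minimum of 10 per arm per site and a total of 120 (Sample size estimation); 10 workers per district (Participant recruitment); t-tests, ANOVA or nonparametric analogs at p < 0.05 (Data analyses). Sidedness is not stated; two-sided is assumed.

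**1. The plan's own figure.** 20 × 3 = 60 per arm and 60 × 2 = 120, as stated. The minimum is 10 × 3 = 30 per arm.

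**2. How far arm and location overlap.** 20 ÷ (5 + 5) = 2 districts per arm per state, so 4 per state and 12 in all. If each state has about two near, trained districts and two distant, control districts, near/far status and arm are the same variable within a state. A model could use only the small differences in distance within each pair, and would have to extrapolate across the gap between pairs.

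**3. Knowledge, post-test compared without the pretest.** Let d be the location gap in SD units. The article gives no value, so d is assumed. With no training effect and n independent workers per arm:

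SE = √(2/n); P(reject) = Φ(d/SE − 1.96) + Φ(−d/SE − 1.96).

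For n = 60, SE = √(2/60) = 0.1826. For d = 0.3, d/SE = 1.643, so P = Φ(−0.317) + Φ(−3.603) = 0.376.

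| Assumed gap (SD) | 60 per arm | 30 per arm |
|---|---|---|
| 0 | 5.0% | 5.0% |
| 0.1 | 8.5% | 6.7% |
| 0.2 | 19.5% | 12.1% |
| 0.3 | 37.6% | 21.3% |
| 0.5 | 78.2% | 49.1% |

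For scale, the difference detectable with 80% power at 60 per arm is (1.960 + 0.842) × 0.1826 = 0.51 SD. In a post-test comparison alone, a location gap of that size would look like a training effect.

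**4. Knowledge, pretest used.** The pretest is taken by both arms, so a gap present before training is measured. An analysis adjusted for pretest score can correct it without separating distance from arm.

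**5. Referrals.** Let k be the referral rate of distant centers relative to near ones, with no training effect. The spurious rate ratio is 1/k. The article gives no k. Assuming 0.8 gives 1/0.8 = 1.25; assuming 0.6 gives 1/0.6 = 1.67. If k = 1 there is no bias. With counts only after training, k cannot be told apart from a training effect. With counts from the 3 months before training, the post/pre ratio in each arm cancels k, provided that referrals would otherwise have changed in the same proportion in both arms.

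**The case against.** Much of the defense stands. The study is declared quasi-experimental, and the Discussion calls the groups nonequivalent, admits selection bias and limits its conclusions to association. Workers with earlier oral health training, nurses in dental and maxillofacial units and those who have helped in cleft programs are excluded, which narrows one route by which near workers could start ahead. Both arms take the pretest, and a baseline comparison is planned. Adjusted analyses may be in an analysis plan that is not shown, so their absence from the article is not held against it.

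Several stronger readings are tempting, but the document does not support them:

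- *The direction of bias is known.* The rule refers to distance from the training center. Nothing says where the dental centers lie, or that the distant districts are rural. The link to dental access is an inference consistent with the Introduction.
- *Every control district is farther away than every trained one.* The rule is relative, and groups are compared within site. It need not hold across states.
- *Separate districts already prevent contamination, so distance was needless.* The article does not show that separate districts would suffice. Geographic separation is a legitimate aim.
- *The false-positive rate is about 37%.* That figure needs an assumed 0.3 SD gap and a post-test comparison that ignores the pretest.

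The general caveat still leaves a gap. It does not name distance, it is followed by an appeal to similarity that the rule gives no reason to expect, and it does nothing for referrals. Nor does separation require that the near side always be the trained side.

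**Conclusion.** The point holds in this form: the rule ties arm to location, so the effect of training and the effect of location cannot be separated, and neither the comparability statement nor the assumed baseline similarity follows from how participants were chosen. Those statements are unsupported rather than flatly contradicted.

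For knowledge, the problem can be repaired with the pretest. The 8.5% to 78.2% range at 60 per arm describes only what happens if the pretest is ignored, under assumed gaps of 0.1 to 0.5 SD and independent observations. For referrals, the problem remains as the plan is described. A spurious ratio of 1.25 to 1.67 rests wholly on the assumed 60–80% relative rate, and a bias toward the trained arm is plausible, not established.

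**What to change.** **If selection is still open.** Keep the arms in geographically separate districts, but draw by lot within each state which district group is trained. The sample stays at 120. The cost is one draw per state and travel for some trainees. With three states there are only 2³ = 8 outcomes, and in 2 of the 8 all three states fall the same way. The draw removes the systematic tilt but does not guarantee balance, so distance should still be reported.

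**If selection is fixed**, as the past tense in Participant recruitment suggests:

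- Delete the comparability wording in Intervention and control, and name distance as a specific limitation in the Discussion.
- Record each health center's distance to the training center and to the nearest dental center, and report both by arm.
- Compare knowledge between arms adjusted for pretest score.
- Retrieve referral counts for the 3 months before training from existing center records, and base the referral conclusion on change from that baseline.
- If those counts cannot be retrieved, report the between-arm referral comparison as descriptive only.

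The wording changes cost nothing, the distances are two recorded variables per center, and the referral counts need modest record retrieval. The article does not say whether such records exist.

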### Intervention and control

The intervention and control groups will consist of participants selected by a non-random process but with comparable characteristics. Across the three study sites, a total of 60 PHC workers (20 Nurses and CHWs at each site) will be assigned to the intervention group, and a corresponding number of participants will constitute the control group. Participants in the control group will receive a one-off conventional oral health education session consisting of a lecture on oral health, tooth brushing, and diet and oral hygiene demonstration using dental models. The intervention group will be exposed to the week-long pilot training on oral health education delivered by designated trainers (see Table 2). They will also participate in group activities such as oral exams and activity sheets. Each module is expected to last for approximately 4 h. Participants in the intervention group (those who will be trained) will be compared to the control group at each study site. Before the training begins, each participant will be administered a pre-intervention questionnaire to evaluate their oral health knowledge at baseline. The assessment will be repeated immediately after training and after 3 months. These evaluations not only serve as a means of monitoring training impact but also allow participants to observe how they improve throughout the training.

**Table 2 tab2:** Program and module delivery for the five-day training.

Day	Module
Day 1	Pre-intervention test Introduction to oral health
Day 2	Introduction to oral diseases and conditions
Day 3	Techniques in oral health promotion and oral disease prevention
Day 4	School and community-based oral health promotion
Day 5	MCOH Post-intervention test Facilitator assessment of participants capability to provide oral health education.

The training modules will include the adaptation of existing training resources - Oral Health Training Course for Community Health Workers in Africa developed by the World Health Organization (WHO),^1^ Oral Health in Comprehensive Cleft Care Educational resources for non-oral health professionals developed by the World Dental Federation (48), and a maternal and child oral health (MCOH) module co-developed by our group consisting of subject matter experts in the field of dental education, dental public health and public health with particular emphasis on stigmatizing conditions such as orofacial clefts and Noma. Participants will be exposed to 4 modules from the OpenWHO course and an additional MCOH module (Table 2). These modules will cover an introduction to oral health, an introduction to oral diseases and conditions, techniques in oral health promotion and oral disease prevention, school and community-based oral health promotion and the MCOH module developed by our group. The OpenWHO course also has a special module that designated trainers will be required to study before the commencement of the training. For this pilot, a member of the research team (an Indigenous local) fluent in the local language at each study site (Hausa and Yoruba) will be designated to provide summaries and interpretation for complex terms. Each group of the participants will also have a designated group lead who will be fluent in both the Indigenous language and in English to also summarize each daily’s training module and direct the associated training activities of the participants. To corroborate dissemination of the training modules, participants will be picked randomly from each group to further explain each module’s concepts to ascertain profound understanding of interpreted complex terms and salient aspects of the training module.

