#### Null hypothesis

No measurable difference will be observed in the post-intervention knowledge scores and referral practices as it relates to oral health between participants with access to the 5-day training workshop vs. the control group.

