### Sample size estimation

For the feasibility of pilot studies, research has shown that a sample size consisting of 30 participants in a group is sufficient (44, 45). Based on this evidence, we plan to recruit a minimum of 10 and a maximum of 20 nurses and community health workers in each group per study site. Overall, the estimated sample size for the quantitative component of this pilot study across the three study sites is 120 (60 participants in the intervention group and 60 participants in the control group). The data obtained from this pilot program will be used to estimate a suitable sample size for our major study in the future (46). For the qualitative assessment, unstructured interviews will be conducted with the trainers. A full-group focus group discussion [>7 participants per group as defined by Cortini et al. (47)] will be conducted at each study site. For this study, we intend to engage 8–10 participants per site.

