### Participants

For each study site, 40 participants (20 interventions and 20 controls) will be selected from a minimum of 4 PHCs. Participant selection will be by cluster sampling in each study site. In order to prevent cross-contamination among the participants, those in the intervention and control groups will be selected from different centers. Eligible participants will be 18 years and older, who speak and respond to questions in English, are employed full-time as a Nurse or CHW at the selected PHCs, have had no previous exposure to oral health training, and be willing to participate in the study. Participants with previous exposure to oral health training and those who cannot commit to the entire duration of the training will be excluded from the study.

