### Data analyses

Quantitative data analysis will be conducted using SPSS version 28. Univariate analysis presenting the frequencies and percentages for categorical variables and the means and standard deviation (SD) for the continuous variables will be performed. For the bivariate analysis, t-tests and ANOVA or their nonparametric analogs (based on normality) will be conducted for within and between group associations with a *p*-value set at <0.05. For the qualitative data analysis, audio recordings obtained during data collection will be transcribed verbatim by the research team and will be analyzed by content analysis. Data will be analyzed using Nvivo12. Responses will be coded into themes and sub-themes, ensuring data saturation when no new information is discovered in data analysis. Comparison, mapping, and verification of conclusions will be conducted and arranged according to the study objectives. Prominent quotes from the participants will be selected and cited within the report.

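### The only stated level of comparison is within each site (20 v 20, minimum 10 v 10), while the hypotheses and sample size concern the whole groups; a pooled, site-adjusted comparison should replace it

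*Protocol article*

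**What the plan says.** Four places in the protocol article bear on the level at which the groups are compared.

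- **Intervention and control:** "Participants in the intervention group (those who will be trained) will be compared to the control group at each study site". No other sentence ties the comparison to a level.
- **Null hypothesis** (and its alternate): "No measurable difference will be observed in the post-intervention knowledge scores and referral practices as it relates to oral health". The contrast is trained workers against controls, and site is not mentioned.
- **Sample size estimation:** "For the feasibility of pilot studies, research has shown that a sample size consisting of 30 participants in a group is sufficient". On that basis, "we plan to recruit a minimum of 10 and a maximum of 20 nurses and community health workers in each group per study site", for a planned total of 120 (60 per group). The Participants section repeats the local figure: "For each study site, 40 participants (20 interventions and 20 controls) will be selected from a minimum of 4 PHCs".
- **Data analyses:** "t-tests and ANOVA or their nonparametric analogs (based on normality) will be conducted for within and between group associations". The only threshold stated for these tests is p<0.05. No pooled comparison and no site term is named.

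**The concern.** The sections point to different analyses. The hypotheses and the size rationale describe one contrast between two whole groups. The sentence on comparison describes a contrast inside each of three sites, and the analysis section does not resolve the difference.

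Two things are at stake if the site-level sentence is followed. First, each comparison uses a third of the participants, so a moderate effect would usually be missed at a single site, and differences between sites would be hard to tell from chance. Second, each outcome is tested three times instead of once at 0.05, which raises the chance of at least one false positive. These are separate problems: small groups cost power and precision, and repeated testing costs error control.

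The pilot's data are also meant to help size a later major study. One pooled estimate with a confidence interval serves that purpose better than three site-level p-values.

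**Working it through.** **Inputs from the document.** Three sites; 20 per group per site planned, with a minimum of 10; 60 per group in total; p<0.05 with no adjustment stated; two outcomes in the hypothesis (knowledge scores and referral practices).

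**Assumptions.** Two-sided tests, 80% power, independent participants and effects in SD units. The article states no power target, effect size, SD or intraclass correlation.

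**Step 1. The plan's own figure.** 3 sites x 20 per group x 2 groups = 120, as stated. At the minimum, 3 x 10 = 30 per group. The 30-per-group figure is therefore reached at the minimum, and doubled at the planned size, when the sites are added together.

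**Step 2. Detectable difference and precision.** The detectable difference d solves power = 0.80 for a two-sample t-test with 2n − 2 degrees of freedom and noncentrality d × √(n/2). The 95% confidence interval half-width is t(0.975, 2n − 2) × √(2/n).

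| Per group | Detectable at 80% power | 95% CI half-width |
|---|---|---|
| 10 (site minimum) | 1.32 SD | 2.101 × 0.447 = 0.94 SD |
| 20 (site, planned) | 0.91 SD | 2.024 × 0.316 = 0.64 SD |
| 60 (pooled, planned) | 0.52 SD | 1.980 × 0.183 = 0.36 SD |

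For an illustrative true effect of 0.5 SD (an assumption), power is about 19% at 10 v 10, 34% at 20 v 20 and 78% at 60 v 60.

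**Step 3. Chance of at least one false positive.** For k independent tests at 0.05 this is 1 − 0.95^k.

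- One outcome at three sites: 1 − 0.95^3 = 14.3%.
- Two hypothesis outcomes at three sites: 1 − 0.95^6 = 26.5%.
- Two hypothesis outcomes, pooled: 1 − 0.95^2 = 9.75%.

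The three sites have different participants, so independence between sites is reasonable apart from any shared influences. Two outcomes within a site may be correlated. In a simulation of six tests with correlations of 0.3 to 0.8 between the two outcomes, the 26.5% becomes about 26% to 22%. The figure is not sensitive to this.

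**The case against.** The strongest reply is that the sentence is not an analysis specification. It stands in the section on the intervention and control conditions, soon after the allocation, and may mean only that each site has its own concurrent control group. The hypotheses do not mention site, and the analysis section does not announce site-by-site tests. This stands as far as intent goes: separate testing is the literal reading, not a certain one. It does not remove the point, because this is the only sentence that fixes the level and it does not match the hypotheses.

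It can also be said that multiplicity rules and model terms are usually left to an analysis plan, and that this is a pilot. That is right, and no fault is found in their absence. The point concerns a comparison the article does state.

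A reader might go further in three ways that the document does not support.

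- **That the plan breaches its own 30-per-group benchmark.** That figure is offered for the feasibility of pilot studies, and the group totals of 30 to 60 meet it. It is not a minimum for a test at one site.
- **That any one significant test would count as success.** No such rule is stated, and the article's references to success are not tied to p-values.
- **That the false-positive chance is about 40%.** A figure of 37% needs nine independent tests (three sites, knowledge twice, referrals once), a count the article does not set out. A simulated 41% for one outcome at three sites assumes clusters of ten with an intraclass correlation of 0.10. It mainly reflects clustering: without it, the same simulation gives about 15%. Pooling alone would still leave roughly 15% to 17% under that assumption.

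**Conclusion.** The point holds as a mismatch to be reconciled, with a better method available. Read literally, the stated comparison gives three contrasts that each detect about 0.91 SD at the planned size (1.32 SD at the minimum), against 0.52 SD for the whole groups. The chance of at least one false positive is about 14% for one outcome, and about 26% for the two hypothesis outcomes, against 9.75% for those two outcomes pooled.

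The detectable differences rest on two-sided 5% tests, 80% power and independent participants. The false-positive figures further rest on independent tests and on each site being tested separately. Participants are drawn from a small number of centres, so clustering could make both sets of figures worse. That is a separate matter, and this point does not rely on it.

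**What to change.** Replace the sentence under Intervention and control with: *The groups will be compared across the three sites combined, with state as a fixed effect and adjustment for the baseline knowledge score.* The baseline adjustment applies to the knowledge outcome and uses the pre-intervention questionnaire already planned for every participant. Report site-specific results as estimates with 95% confidence intervals and without significance claims, and align Data analyses with this.

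Whether the immediate or the 3-month assessment leads is for the sponsor to choose; the document gives no ground for preferring either.

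The cost is wording only: recruitment, training and data collection do not change. The downside is that no significance statement can be made for a single site. The change does not deal with clustering by centre, which needs its own treatment.
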